#### Secondary hypotheses

Hypothesis 2.1: PROMs correlate more strongly with quantitative functional parameters including muscle fatigue, spinal load and biomechanical parameters or lumbopelvic range of motion during forward trunk bending and during walking than with pathomorphological parameters including severity of stenosis, segmental instability and muscle degeneration.

Hypothesis 2.2: Changes in PROMs correlate with changes in static and dynamic spinal imbalance, muscle fatigue and extent of forward trunk bending, lumbopelvic range of motion during walking and spinal loads from before to after spinal stenosis surgery.

Hypothesis 2.3: Patients with sLSS with greater muscle degeneration and greater spinal imbalance have greater muscle fatigue.

Hypothesis 2.4: At follow-up, patients with spinal stenosis will have improved PROMs, less static and dynamic spinal imbalance and muscle fatigue, and less forward trunk bending and larger lumbopelvic range of motion during walking than before spinal stenosis surgery.

Hypothesis 2.5: Postoperative PROMs are explained by preoperative severity of LSS, spinal alignment, segmental instability, muscle degeneration, dynamic compensation, muscle fatigue and spinal load.

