#### **3.3 Study procedures**

After the patients' arrival at the movement laboratory, the patient is informed in detail about all study procedures. If there are no questions from the patient, the informed consent form is signed. Subsequently, clinical and demographic parameters including age, body mass, body height, pain medication, previous treatment (physiotherapy, infiltration, other), duration of symptoms and own physical exercise program will be recorded on the case report file. In a next step, participants will

be asked to complete several PROMs questionnaires including the validated German versions of the ODI, EQ-5D-5L, Swiss Spinal Stenosis Questionnaire, Tampa scale of kinesiophobia and Spine Tango COMI. PROMs will be digitally collected using iPads and surveys created on the REDCap® [22] web application for building and managing online surveys and databases (approximate duration: 15 minutes).

After completion of the questionnaires, all participants will be prepared for the functional biomechanical analysis, which starts with a clinical measurement of the active and passive range of motion of ankle, knee and hip joints. This also includes a neurological examination of the key muscles according to Janda, and a test used to elicit Trendelenburg signs. Next, the back performance scale movement assessment will be performed. The assessment includes five separate tests (Sock Test, Pick-up Test, Roll-up Test, Fingertip-to-Floor Test, and Lift Test) that will only be performed if allowed by the patients' current pain situation (approximate duration: 30 minutes).

Prior to placement of surface EMG electrodes, specific skin areas will be shaved and cleaned, if necessary. Electrodes will be placed on selected abdominal and paraspinal muscles. Reflective markers will be placed on anatomical landmarks (approximate duration: 45 minutes).

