Participants will be handed out activity monitors after test-day one and test-day two. The same activity monitor will be sent to study participants six months after the spine surgery. Participants will be asked to wear the activity monitor for nine days on their wrist. Participants will be given prepaid envelopes to return the devices. In addition, participants will be asked to complete a digital set of PROMs six months after the spine surgery sent to them via e-mail. If no e-mail address is available, printed versions will be sent together with the activity monitor.

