violation of this assumption in the data we will use more appropriate statistical methods (e.g., nonparametric methods). Our predictive model building approach will be based on the seven steps of Steyerberg's [45] to construct a predictive model to predict the surgical outcome from preoperative clinical, functional, radiological, and biomechanical data and musculoskeletal model prediction of postoperative local spinal loads. Data will be checked for accuracy, inconsistencies, and plausibility of the recorded information in the data, and if required re-coding/re-grouping of certain variables will be done. We will restrict categorizing the continuous variables in the model development stage as much as possible to avoid loss of information and assess the predictive ability of the clinically relevant variables (e.g., from preoperative – spinal alignment, segmental instability, muscle degeneration, dynamic compensation, muscle fatigue, and biomechanical parameters) and variables with good/high predictive performance will be used to construct the predictive models. A different set of predictive models will be set up using the candidate predictors with the outcome PROMs. We will compare the predictive performance of the models to select the best-performed model using appropriate statistical methods (e.g., R^2). The predictive models will be based on collected experimental data and also simulated data. As a few of the highly clinically relevant variables cannot be measured directly we will use the experimental data to simulate these variables. For the internal validation of the selected predictive model, we will use cross-validation.

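### Hypothesis 2.5 names seven preoperative factors, but section 4.2 addresses it with a performance-selected prediction model that never estimates the seven together and leans towards confirmation

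*Protocol*

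**What the plan says.** Hypothesis 2.5 (Protocol 2.1, Secondary hypotheses) reads: "Postoperative PROMs are explained by preoperative severity of LSS, spinal alignment, segmental instability, muscle degeneration, dynamic compensation, muscle fatigue and spinal load". That is a statement about a closed list of seven factors.

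Section 4.2 answers it with a prediction-model exercise. Candidate variables are assessed for predictive ability, and "variables with good/high predictive performance will be used to construct the predictive models". Then "A different set of predictive models will be set up using the candidate predictors with the outcome PROMs", and "We will compare the predictive performance of the models to select the best-performed model", with R² given as an example of the yardstick. The selected model is then cross-validated. The candidates are illustrated by a bracket that begins "e.g., from preoperative – spinal alignment, segmental instability, muscle degeneration, dynamic compensation, muscle fatigue, and biomechanical parameters".

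On the outcome, section 3.3 lists "several PROMs questionnaires including the validated German versions of the ODI, EQ-5D-5L, Swiss Spinal Stenosis Questionnaire, Tampa scale of kinesiophobia and Spine Tango COMI", which is five instruments. Besides the one-year visit, "participants will be asked to complete a digital set of PROMs six months after the spine surgery". Section 2.2 makes the ODI a primary endpoint.

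**The concern.** A hypothesis about a fixed set of factors needs an analysis in which that set is fitted and reported whatever the result. A performance-driven search answers another question: which subset of the available variables predicts best in this sample. Two consequences follow from the stated rule.

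- A named factor that performs poorly is removed before the final model is built. That model cannot show that the factor fails to explain outcome, nor what it contributes once the other six are accounted for.
- The variables that remain were kept because they looked good in the same data. A favourable R² or test of that model overstates the support for Hypothesis 2.5.

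The outcome adds to this. With five PROMs, two postoperative collection times and no named lead in the modelling text, nothing stops the PROM itself from being chosen because it was predicted best, although R² values for different outcomes are not comparable.

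**Working it through.** **Hypothesis and analysis side by side.** Hypothesis 2.5 has seven factors: stenosis severity, spinal alignment, segmental instability, muscle degeneration, dynamic compensation, muscle fatigue and spinal load. Section 4.2 contains no step in which these seven enter one model together. Its correlations and ANOVA take one variable at a time and are not tied to postoperative PROMs. The protocol gives no figure, cut-off or decision criterion for Hypothesis 2.5, so there is nothing to reproduce. What follows is illustration.

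**Inputs.** Evaluable patients: 122 × 0.9 = 109.8, taken as 110 (section 4.1). Factors: 7 (Hypothesis 2.5). PROMs: 5 (section 3.3). Assumptions not in the protocol: one variable per factor, correlations of 0.2 among factors, and the screening rules below.

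**No true effect, one PROM.** As a hand check, with seven independent null variables and a univariable screen at p < 0.05, the chance that at least one passes is 1 − 0.95^7 = 0.302. A model built only from variables that passed is nearly always nominally significant. Simulation (4,000 runs per setting, F-test of the resulting model at 5%):

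| Rule | Nominally significant |
|---|---|
| Keep p < 0.05 | 28.8% |
| Keep p < 0.20 | 27.9% |
| Keep best three | 19.4% |
| All seven, fixed | 4.9 to 5.5% |

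Independent repeats agree to within two or three percentage points.

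**True factors lost.** Take three uncorrelated factors, each with a true standardised effect of 0.2, and a p < 0.05 screen. By Fisher's z, atanh(0.2) × √(110 − 3) = 0.2027 × 10.34 = 2.10, and Φ(2.10 − 1.96) ≈ 0.55. Simulation gives 55 to 57%. Each real factor is therefore dropped in roughly 44% of studies.

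**If the PROM were also chosen by fit.** With all seven null variables fixed and the best of five PROMs taken, the error rate is 20.2%, 17.2% and 13.5% for correlations between PROMs of 0.4, 0.6 and 0.8.

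**Does cross-validation repair it?** Null simulation (300 runs, seven independent variables, p < 0.05 screen, 10 folds), share of all runs with cross-validated R² above zero:

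| | Only the selected model validated | Screen repeated in each fold |
|---|---|---|
| One PROM | 27% | 6% |
| Best of five PROMs (correlated 0.6) | 65% | 20% |

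In the second column any choice between PROMs still lies outside the folds. Validating only the model already selected, as section 4.2 words it, leaves most of the selection effect in place.

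**Power of the fixed model.** Joint F-test of seven terms with preoperative ODI as a further covariate: residual df = 110 − 7 − 1 − 1 = 101. At an assumed partial R² of 0.13, f² = 0.13/0.87 = 0.149 and λ = 0.149 × 110 = 16.4, giving power 0.83. At partial R² 0.10 (λ = 12.2) it is 0.68, and at 0.15 (λ = 19.4) it is 0.90. If stenosis severity takes two indicator terms (8 df, residual 100), power at 0.13 is 0.81; with three (9 df, residual 99) it is 0.78.

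**The case against.** The best reply has five parts.

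- **Confirmation is not guaranteed.** A reader might infer that Hypothesis 2.5 can be confirmed but never refuted. The figures do not support that: roughly 70 to 80% of null studies still give no significant model, and the planned cross-validation can show no predictive value. What stands is a bias towards confirmation.
- **Stenosis severity is not shown to be excluded.** It is absent from "spinal alignment, segmental instability, muscle degeneration, dynamic compensation, muscle fatigue, and biomechanical parameters", and a reader might infer that it has been dropped. But that list is introduced as examples, the predictor pool includes preoperative radiological data, and section 2.2 lists severity as a radiological parameter. The protocol merely does not guarantee that it enters the model.
- **Choosing the PROM by R² is only one reading.** The text can equally mean competing models within each PROM. What stands is that it does not rule out the other reading.
- **Other analyses exist.** The correlations and the ANOVA of severity are not conditional on performance. They are, however, one factor at a time and not linked to postoperative outcome, so they do not replace a joint model.
- **Details may sit in an SAP that is not shown, and the simulated screens are not in the plan.** Both are fair. A missing cut-off, PROM or time point alone would be no finding. But performance-based retention and best-model choice are positive commitments in section 4.2, and an SAP would have to depart from them to estimate the seven factors together.

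**Conclusion.** The point holds as a mismatch between hypothesis and method. Hypothesis 2.5 concerns seven named factors taken together; section 4.2 commits to a search that retains by performance, never estimates the seven jointly and leans towards a favourable answer. The mismatch rests on the protocol's wording alone. Its size rests on assumptions: about 20 to 30% nominally significant models under no effect, against 5% for a fixed model, with 110 patients, one variable per factor and the screens shown. Another retention rule would give another figure. The further 14 to 20% applies only if the PROM is also chosen by fit, which the protocol neither states nor rules out. Hypothesis 2.5 is secondary and the study observational, so this is a change that should be made; it does not threaten the primary analysis.

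**What to change.** In section 4.2, address Hypothesis 2.5 with one model fixed in advance:

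- Outcome: one-year ODI, adjusted for preoperative ODI.
- Predictors: one prespecified variable for each of the seven factors, including stenosis severity coded as categorical or ordinal, with degrees of freedom to match.
- All factors kept whatever their performance, with one joint test and every coefficient with its 95% confidence interval.
- The same model for the other PROMs as secondary results, without choosing between them.

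Keep the performance-selected prediction model as a separate exploratory product that does not decide Hypothesis 2.5, and repeat the selection inside the cross-validation.

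The cost is protocol and SAP wording plus one extra regression, repeated per PROM, on data already collected. The drawbacks are that the variables must be named beforehand, which forces a choice where a factor such as alignment has several parameters, and that the result may look less favourable. A joint test does not by itself refute any single factor, so the coefficients and their intervals need to be reported with it.

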### II. Dynamic compensation

Dynamic compensation is defined as the difference between static and dynamic sagittal spinal alignment. Six possible gait events are available to choose from for the definition of dynamic sagittal spinal balance (left and right; heel-strike, toe-off, midstance). Dynamic sagittal spinal balance may be defined as sagittal spinal balance during left/right midstance, left/right heel strike and/or left/right toe off. Depending on the research question, we will adapt the workflow and use the most appropriate gait event to calculate dynamic sagittal spinal balance.

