### III. Sagittal spinal balance and spinal loads assessed using motion capture

The curvature of the lumbar and thoracic spine during stance and during walking will be computed from the marker data using MATLAB™ (R2021b, The Mathworks Inc., Massachusetts, USA) software. A cubic polynomial function will be fitted to the marker positions in each time frame, approximating an S-shaped spine curvature with thoracic kyphosis (TK) and lumbar lordosis (LL) curves [1]. The workflow used to calculate sagittal spinal balance parameters is based on the calculation methods for radiological sagittal spinal balance parameters and was established and tested in a previously conducted pilot study (EKNZ Project ID 2021-02012). The set of marker-based sagittal spinal balance parameters comprises LL, TK, sagittal vertical axis (SVA), spino-sacral angle (SSA), spine inclination (SI) (Figure 3).

[figure not shown]

**Figure 3:** Computed Marker Data and Calculation of Sagittal Spinal Balance Parameters [1]

The data obtained using motion capture will be used to estimate spinal load using musculoskeletal modeling [28].

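### Section 4.2 cross-validates only the model already selected, so followed as written the reported R² for Hypothesis 2.5 will tend to be too high

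*Protocol*

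**What the plan says.** The prediction model serves Hypothesis 2.5 (Protocol section 2.1): "Postoperative PROMs are explained by preoperative severity of LSS, spinal alignment, segmental instability, muscle degeneration, dynamic compensation, muscle fatigue and spinal load". Section 4.2 describes the model building in this order:

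1. Candidates are assessed for predictive ability, and "variables with good/high predictive performance will be used to construct the predictive models".
2. Several models are built: "A different set of predictive models will be set up using the candidate predictors with the outcome PROMs".
3. One is chosen: "We will compare the predictive performance of the models to select the best-performed model using appropriate statistical methods", with R² given as an example.
4. The section then ends: "For the internal validation of the selected predictive model, we will use cross-validation".

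The section gives no number of candidates, screening threshold, number of models or number of folds. It mentions no hold-out sample, nesting, bootstrap of the procedure or optimism correction. It does cite a seven-step prediction-modelling framework as the basis of the approach.

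**The concern.** Cross-validation is honest only if the left-out patients had no part in building the model that is tested on them. Steps 1 and 3 both use outcomes. If they are done once, before the folds are formed, each left-out patient has already helped to choose the predictors and the model. Cross-validation then corrects for estimating the coefficients but not for the selection, and its R² tends to exceed what new patients would show.

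The candidate pool could be large relative to the sample. Hypothesis 2.5 names seven domains, and several of them hold many variables. For motion-capture alignment, "The set of marker-based sagittal spinal balance parameters comprises LL, TK, sagittal vertical axis (SVA), spino-sacral angle (SSA), spine inclination (SI") gives five. For dynamic compensation, "Six possible gait events are available to choose from for the definition of dynamic sagittal spinal balance", so five parameters at six events allow up to 5 × 6 = 30 variants. Muscle measures are taken by level and side.

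Cross-validation is the only validation of the model that the protocol describes. If it is biased, nothing later in the plan would show it.

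**Working it through.** The protocol states no predictive-performance figure, so there is none to reproduce. The check is whether the stated order biases the result, and by how much.

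**Inputs from the protocol.** Section 4.1 requires 111 patients and enrols 122 with 10% drop-out; 122 × 0.90 = 109.8. The simulations use n = 110 or 111.

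**Assumed inputs.** Number and correlation of candidates, selection rule, linear regression, 10 folds, and population R² (0, or 0.20 from 3 or 4 true predictors).

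**Quantities compared**

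- (a) *After selection*: predictors chosen once on all patients, then 10-fold cross-validation of that model. R² = 1 − Σ(y − prediction)² / Σ(y − training mean)².
- (b) *Inside folds*: the same, but with selection repeated in each training set.
- (c) *True*: R² of the final model in new patients. For independent candidates with residual variance 1 this is 1 − [1 + Σ(β − b)² + b₀²] / [1 + Σβ²]. With three true predictors and R² = 0.20, each β = √(0.20/0.80/3) = 0.289, and the outcome variance is 1.25.
- Excess = (a) − (c).

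**Rule 1: keep the m candidates most correlated with the outcome** (n = 111, independent candidates, 600 runs)

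| Candidates, kept | Population R² | (a) | (b) | (c) | Excess |
|---|---|---|---|---|---|
| 7, 3 | 0.20 | 0.170 | 0.141 | 0.141 | 0.029 |
| 10, 5 | 0.20 | 0.170 | 0.126 | 0.131 | 0.039 |
| 20, 5 | 0.20 | 0.186 | 0.094 | 0.105 | 0.081 |
| 40, 5 | 0.20 | 0.202 | 0.058 | 0.069 | 0.133 |
| 60, 8 | 0.20 | 0.224 | 0.005 | 0.024 | 0.200 |
| 7, 3 | 0 | −0.004 | −0.061 | −0.064 | 0.060 |
| 10, 5 | 0 | −0.017 | −0.090 | −0.090 | 0.073 |
| 20, 5 | 0 | 0.027 | −0.124 | −0.127 | 0.154 |
| 40, 5 | 0 | 0.075 | −0.159 | −0.166 | 0.241 |
| 60, 8 | 0 | 0.099 | −0.234 | −0.224 | 0.323 |

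**Rule 2: keep candidates with univariable p < 0.10** (n = 110, independent candidates, 400 runs)

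| Candidates | Population R² | (a) | (c) | Excess |
|---|---|---|---|---|
| 7 | 0.20 | 0.153 | 0.120 | 0.033 |
| 10 | 0.20 | 0.153 | 0.112 | 0.041 |
| 30 | 0.20 | 0.178 | 0.063 | 0.115 |
| 40 | 0.20 | 0.184 | 0.046 | 0.138 |
| 30 | 0 | 0.039 | −0.117 | 0.156 |
| 40 | 0 | 0.054 | −0.147 | 0.201 |

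A separate run at n = 111 (200 runs) gave an excess of about 0.03, 0.05 and 0.12 with 7, 10 and 35 independent candidates at population R² 0.20. With no signal it gave about 0.03 to 0.17.

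**Correlated candidates.** The protocol's variables overlap, so 35 candidates in seven blocks of five were also tried.

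- With within-block correlation 0.5 to 0.7 and population R² 0.20, the excess was about 0.01 to 0.06.
- A further set at correlation 0.5, using p < 0.10, p < 0.05 and best-five selection, gave (a) 0.12 to 0.15 against (c) 0.055 to 0.060. That is an excess of roughly 0.06 to 0.09, so the upper end depends on the selection rule.
- With no signal, (a) was about 0.00 to 0.02 against (c) of about −0.09 to −0.13.

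**Reading.** (a) exceeds (c) in every scenario tabulated, while (b) stays within about 0.02 of (c) in the first table. The excess therefore comes from doing the selection outside the folds. These runs cover predictor screening only and leave out the further choice among models.

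**The case against.** The strongest reply is that the fault is partly inferred. A reader might infer that the protocol commits to selecting on the full data, or rules out nesting. It says neither. A separate analysis plan may exist, and the cited framework may lead the analyst to resample the whole procedure. This stands as a limit on certainty, but it does not remove the point. Section 4.2 is not silent: it sets out an order and names the already selected model as the thing to be validated.

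Four stronger readings are tempting and are not supported:

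- *That choosing by R² always favours the largest model.* The text offers R² only as an example and does not say it is the in-sample value. Even in-sample R² is bound to rise only between nested models, and the planned models need not be nested.
- *That the excess must be large.* With seven to ten candidates it is a few hundredths, and correlation among candidates reduces it. In one artificial case (35 equally correlated candidates, a real signal and loose screening that kept more than 20), cross-validation after selection erred downward.
- *That a worthless model would look useful.* At p < 0.10 with 30 to 40 candidates and no signal, R² after selection is only 0.04 to 0.05. It is wrongly positive, but few would call it useful.
- *That treatment decisions hang on it.* Section 1 does aim at treatment planning, but it makes this conditional on confirming relationships with spinal load and refers to the framework as a whole. Section 6.2 says participation does not influence treatment.

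**Conclusion.** The concern holds in this form: followed in the order that section 4.2 gives, the internal validation omits the optimism from predictor screening and model choice, and the R² reported for Hypothesis 2.5 will tend to be too high.

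The direction follows from the stated order. The size cannot be fixed from the document. At about 110 patients with p < 0.10 screening, the excess over true R² is:

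- population R² 0.20, 7 to 10 independent candidates: about 0.03 to 0.05;
- population R² 0.20, 30 to 40 independent candidates: about 0.12 to 0.14;
- population R² 0.20, 35 correlated candidates: about 0.01 to 0.06, and somewhat more under other selection rules;
- no signal: about 0.03 to 0.20.

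This concerns one secondary hypothesis; Hypothesis 1 and the sample size do not depend on it. It should be corrected before the model is built, because the correction is cheap and the plan has no later safeguard.

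**What to change.** Replace the last sentence of section 4.2 with:

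*Internal validation will repeat all data-driven steps (variable screening, outcome-driven re-grouping, and choice between models) within every training fold (nested cross-validation) or bootstrap sample. Models will be compared on cross-validated or optimism-corrected performance, and that corrected performance will be reported.*

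Re-coding that only corrects implausible entries, without reference to the outcome, can stay outside the folds.

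The cost is a little programming time, with no change to patients, visits or measurements. The reported R² will be lower. Penalised regression in place of screening, and reporting a calibration slope, are reasonable options but are not needed to correct this point.
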